# Effects of Time-Restricted Eating on Ketone Metabolism and Immunoregulation in Premenopausal Women: Protocol for a Pilot, Prospective, Single-Arm Dietary Intervention Study

**DOI:** 10.2196/81063

**Published:** 2026-03-06

**Keywords:** time-restricted eating, intermittent fasting, ketones, immune cells, immunology

## Abstract

**Background:**

Intermittent fasting interventions, such as time-restricted eating (TRE) without calorie restriction, may offer diverse cardiometabolic health benefits, including reductions in inflammation. However, the underlying metabolic mechanisms are poorly understood.

**Objective:**

This study is designed to evaluate ketone metabolism and immunoregulation during TRE (6-hour feeding and 18-hour fasting) without caloric restriction compared to a conventional dietary regimen (12-hour feeding and 12-hour fasting) in women.

**Methods:**

This is a pilot, prospective, single-arm dietary intervention study in premenopausal women classified as lean and obese, with intraindividual and stratified comparisons. Ketone turnover, immunologic responses, and metabolic profiles will be compared between a conventional dietary regimen (12-hour feeding and 12-hour fasting) at admission and after 3 days of TRE (6-hour feeding and 18-hour fasting).

**Results:**

The trial commenced in August 2024. As of February 2026, participant enrollment is ongoing. Complete enrollment is expected in the December 2026. Integrated analyses will be reported once data analysis is completed, which is expected in the winter of 2027.

**Conclusions:**

This clinical protocol will evaluate whole-body ketone metabolism and immunoregulatory changes in women during TRE using state-of-the-art stable isotope and immunophenotyping techniques. This study will determine the effects of a time-limited dietary pattern, without caloric restriction, on dynamic measures of immunity and metabolism.

**Trial Registration:**

ClinicalTrials.gov NCT06169137; https://clinicaltrials.gov/study/NCT06169137

**International Registered Report Identifier (IRRID):**

DERR1-10.2196/81063

## Introduction

### Background

Time-restricted eating (TRE) is a popular form of intermittent fasting, an eating pattern that alternates between eating and fasting within defined daily eating windows (4-10 h). Early TRE dietary patterns confine eating windows to the daylight waking hours with or without caloric or macronutrient restriction [1]. TRE has been linked to multiple metabolic and immune benefits, including antiaging and longevity benefits [2], healthy body weight, improved insulin sensitivity, and reduced glucose excursions in healthy and overweight individuals [3-11]. TRE has also been associated with changes in thyroid function, menstrual regularity, fatty acid metabolism, and neuroendocrine stress responses, particularly when associated with energy deprivation [12-15].

The underlying mechanisms mediating these metabolic benefits of TRE have not yet been elucidated. Chronic fasting may extend longevity and reduce inflammation [13,14,16]; however, whether shorter fasting durations during TRE modulate immune activation to promote healthy metabolism remains unclear. Fasting-induced ketogenesis during intermittent fasting regimens may be a key mediator of the anti-inflammatory response associated with TRE [17]. Physiological ketosis is protective and homeostatic in contrast to pathological states such as diabetic ketoacidosis [18]. Canonically, ketone bodies are a critical energy source for the brain during periods of diminished glucose availability during prolonged fasting [19]. However, contemporary data suggest that elevated circulating ketone bodies are also key signaling molecules and epigenetic or posttranslational modifiers [19].

Ketone bodies (acetoacetate and β-hydroxybutyrate [βOHB]) interact with various histone deacetylases and other proteins to induce posttranslational modifications, reduce oxidative stress, and inhibit the activation of the nucleotide-binding oligomerization domain–like receptor family pyrin domain containing 3 inflammasome [18,20-22]. Notably, βOHB activates transcription factors and adenosine monophosphate–activated protein kinase signaling, which plays a crucial role in regulating inflammatory pathways [23-25]. During a 24-hour fast in healthy individuals, we demonstrated that fasting blunted inflammatory markers and immune activation in monocytes or macrophages and CD4^+^ T cells both in healthy individuals and in those with mild inflammatory disease (steroid-naive asthma) [26,27]. In a small pilot study of men and women with multiple sclerosis, alternate-day intermittent fasting with caloric restriction was associated with gut microbiome remodeling and immune changes suggestive of reduced interleukin-17 (IL-17)–producing T cells and increased numbers of regulatory T cells [28].

Although prolonged fasting durations have been associated with T cell differentiation, whether the 18-hour fasting component of a TRE dietary pattern would be sufficient to induce changes in ketone metabolism and T cell activation is unexplored. An early 6-hour TRE was associated with increased fat oxidation [5] and increased βOHB concentrations by 0.03 (SE of mean 0.01) mM using a crossover 4-day design [4]; however, no studies have linked ketogenesis during TRE with T cell immunophenotyping. Additionally, variations in the metabolic effects of TRE may be confounded by other biological factors; the ketogenic response to TRE may vary according to biological sex and obesity status. Individuals with obesity, compared to lean individuals, have lower rates of ketogenesis, and this may potentially be influenced by nonalcoholic fatty liver disease [29-31]. Moreover, some studies report higher ketogenesis in women than in men [32-35].

### Research Gap and Significance

No studies have examined the metabolic mechanisms of ketone body metabolism and the anti-inflammatory effects of a 6-hour TRE regimen stratified by sex and obesity status. Given the limited research and discrepant findings regarding the effects of biological sex and obesity on ketone turnover, it is crucial to understand their role in response to dietary interventions. This clinical translational study uses state-of-the-art stable isotope and immune-metabolic phenotyping techniques to determine the impact of shifts in nutrient access and availability on dynamic changes in whole-body and cellular ketone turnover and immune activation in healthy women stratified by obesity status. This protocol complements the previous study conducted in men (NCT04728165) and will be used to explore TRE-mediated immune response in men and women.

### Study Aims

#### Primary Aim 1

The first primary aim is to quantify whole-body βOHB turnover after short-term early 6-hour TRE compared to a conventional 12-hour dietary regimen in women.

#### Primary Aim 2

The second primary aim is to quantify CD4^+^ T cell responses after short-term early 6-hour TRE compared to a conventional 12-hour dietary regimen in women.

#### Secondary Aim 1

The first secondary aim is to quantify changes in postabsorptive glucose rate of appearance (R_a_), measured using (6,6-^2^H_2_) glucose and βOHB R_a_ (intravenous), after 3 days of 6-hour TRE.

#### Secondary Aim 2

The second secondary aim is to quantify CD4^+^ T cell responsiveness (T helper 17 [Th17] polarization) in lean versus obese women after 3 days of 6-hour TRE.

## Methods

### Study Setup

This single-site 5-day inpatient study is a pilot, prospective, single-arm intervention trial in premenopausal women classified as lean or obese, with intraindividual and stratified comparisons. Ketone turnover and immunologic responses will be compared between a conventional dietary regimen (12-hour feeding and 12-hour fasting) at admission and after 3 days of TRE (6-hour feeding and 18-hour fasting; Figure 1). Each participant will serve as their own control, with analyses stratified by obesity classification. We chose a 3-day TRE intervention to determine the acute effects of this dietary pattern on ketone metabolism and immune function. Our previous publications showed that a 3-day TRE in men was feasible and improved glycemic variability and hepatic insulin resistance [36,37]. This study was designed to replicate and validate the 3-day TRE and extend these findings by evaluating glycemia and immunometabolism in women and examining ketone-mediated mechanisms. Secondary measures of glucose metabolism will be compared between groups at the same time points. To explore potential effects on hormonal mediators, circadian rhythms, and cardiometabolic markers, these measures will be evaluated at admission and after intervention. This study will be conducted in the Metabolic Clinical Research Unit at the National Institutes of Health (NIH) Clinical Center, Bethesda, Maryland.

**Figure 1 figure1:**
[figure not shown]
Study schema and timeline. Overview of the study design and timeline across screening, conventional diet, and time-restricted eating phases.

### Participants

Healthy premenopausal women aged 18 to 50 years of all races and ethnicities will be recruited. A full overview of inclusion and exclusion criteria is provided in Textbox 1. An overview of recruitment strategies is provided in Textbox 2. Interested participants will complete an online interest questionnaire and telephone interview before screening. (Figure 2).

Study inclusion and exclusion criteria.
**Inclusion criteria**
Willingness to comply and be available for study proceduresWomen aged between 18 and 50 years in their premenopausal phase (regular menses and follicle-stimulating hormone is below the upper limit of normal)BMI of 18 to 24.9 kg/m^2^ or 30 kg/m^2^ or greaterIn good health per medical history and screening laboratory evaluationAgreement to adhere to lifestyle considerations throughout the study
**Exclusion criteria**
Immune, inflammatory, or metabolic conditions that could affect study outcomes, except chronic, controlled hypothyroidismCurrent use of antihyperglycemic medications; systemic steroids; adrenergic stimulants; or drugs affecting sleep, circadian rhythms, or metabolismCaffeine intake more than 300 mg daily (approximately three 8-oz cups of coffee)Factors affecting circadian rhythms, including shift work, irregular sleep or eating schedules, or fasting for more than 15 hours per dayHistory of an eating disorderFood allergies, intolerances, or dietary patterns that restrict consumption of the metabolic dietInability to provide informed consentPregnancy or lactationUnstable body weight, defined as more than 5% change in the past 3 monthsCompetitive sports training or unwilling to follow exercise protocolAlcohol intake of more than 3 servings per dayCurrent smoker or regular tobacco, vaping, or nicotine use within the past 3 months

Recruitment strategies.
**Recruitment strategies**
ClinicalTrials.govClinical Center Research Studies websiteTwitter posts and chats with study investigatorsSocial media posts in accordance with National Institutes of Health (NIH) Social Media GuidelinesUse of the NIH Clinical Center Office of Patient Recruitment services, including the creation and distribution of study flyers and dissemination of information through preexisting recruitment avenues, such as the NIH recruitment listserve

**Figure 2 figure2:**
[figure not shown]
Study flow diagram. Participant recruitment, screening, and study completion. NIH: National Institutes of Health.

### Screening Visit

Study participants will be screened after a 10- to 12-hour overnight fast to confirm eligibility. Screening evaluation will occur within 60 days of the inpatient visit and include obtaining a medical history, physical examination, fasting blood sampling, urine pregnancy testing, anthropometric measurements, resting energy expenditure measured by indirect calorimetry using the ventilated hood technique (Parvo Medics TrueOne 2400), and a nutrition assessment with nutrition research staff. Participants will be asked to complete 3 to 7 days of food logs before their inpatient visit.

The continuous glucose monitoring device (Dexcom, Inc) will either be provided at the screening visit (if eligibility is confirmed) or mailed to the participant approximately 1 week before admission. During the screening visit, participants will receive instructions on how to insert the US Food and Drug Administration–approved continuous glucose monitoring. Device placement instructions will also be reviewed during an in-person or virtual (telehealth) session with a clinician or qualified designee, including guidance on inserting the subcutaneous sensor and attaching the removable transmitter used to measure interstitial glucose levels. Participants will be asked to place the device at home 12 to 24 hours before admission and to wear it throughout their inpatient stay.

### Inpatient Study Visit

Figure 1 outlines the study procedures. On admission to the metabolic unit on day 0, participants will be provided a conventional dietary regimen (09:30 AM to 09:30 PM). A dual-energy X-ray absorptiometry scan (Lunar iDXA; GE HealthCare) will be performed on day 0 to measure fat mass and lean body mass (LBM). Point-of-care ketone levels will be checked every morning using the Precision Xtra Ketone Meter (Abbott Diabetes Care Inc). Surveys will be administered to assess outcomes, including hunger and fullness, appetite, stress, and self-reported positive affect or well-being [38-46]. Participants will have 30 minutes of scheduled light-to-moderate physical activity, involving treadmill walking at a speed calculated to target 35% to 45% of heart rate reserve, using their age-predicted maximum heart rate and resting heart rate obtained during their screening visit.

### TRE Intervention Design

The TRE intervention is a 6-hour early eating window from 09:30 AM to 02:30 PM and will be initiated for 3 consecutive days (days 1-3). Participants will have a 60-minute window to consume each meal (Figure 1). Participants will be asked to consume meals in their entirety, and any foods or beverages not consumed will be reweighed and recorded for data purposes. Eucaloric metabolic breakfast, lunch, and dinner will be provided; each meal is estimated to provide 33% of an individual’s estimated energy needs and a macronutrient distribution of 50% carbohydrate, 35% fat, and 15% protein (Figure 1). Standard breakfast, lunch, and dinner options will be offered from a menu designed by nutrition research team members. Sample menu options are shown in Figure 3.

**Figure 3 figure3:**
[figure not shown]
Illustration of a sample menu with available options. (A) Conventional dietary regimen (day 0). (B) Time-restricted eating dietary regimen (days 1-3).

### Intervention Preparation

Metabolic meals will be prepared at the NIH Clinical Center in the Metabolic Kitchen. Diets will be designed by nutrition research team members using ProNutra diet planning software (Viocare, Inc) to align with a specified macronutrient distribution and total energy provision, informed by indirect calorimetry and an activity factor of 1.4.

### Adherence Monitoring

As an inpatient intervention protocol, this study will monitor and confirm dietary compliance through food weigh backs (as applicable) and detailed case report forms completed by the clinical research study team and clinicians.

### Tracer Administration

On days 1 and 4, participants will receive a fasting 3-hour peripheral infusion of a stable isotope-labeled ketone body and glucose with blood draws obtained at scheduled intervals to trace ketone and glucose metabolism (Figure 4). Ketone body and glucose turnover will be measured using stable isotope tracers. Glucose and βOHB R_a_ will be measured using a primed continuous 3-hour infusion. The (6,6-^2^H_2_) glucose dose will be 0.49 µmol/kg LBM per minute for 180 minutes, with a priming dose of 29.4 µmol/kg LBM, and the (U-^13^C_4_) βOHB will be administered as 1.8 µmol/kg LBM per minute priming dose (10-minute infusion), followed by 0.18 µmol/kg LBM per minute for 170 minutes. Blood samples will be collected before stable isotope administration and during the near–steady-state period (last 30 minutes of the infusion). Whole blood will be centrifuged, and plasma will be transferred and frozen at –80 °C until analysis. Blood samples will be collected for the measurement of glucose, insulin, C-peptide, and ketone bodies. Intravenous stable isotopes will meet NIH minimum standards for stable isotope administration and will be obtained through an NIH-approved pharmacy compounding vendor.

**Figure 4 figure4:**
[figure not shown]
Tracer study protocol. Schematic overview of tracer infusion, blood sampling, and timing relative to the time-restricted eating protocol. βOHB: β-hydroxybutyrate.

### Sample Size Justification

Sample size determination is based on the ability to detect meaningful differences in ketone-body turnover and CD4^+^ T cell responsiveness and determine effect sizes for short-term TRE. Because calculations are derived from limited past data, variances are anticipated, and the sample size calculations are feasibility estimates.

The primary outcomes are as follows: (1) change in βOHB R_a_ to determine the effect of short-term TRE on ketone-body metabolism (2) change in CD4^+^ T cell responsiveness (T helper type 1, T helper type 2, Th17, and Treg cytokines)

These outcomes will be evaluated using a 2-sided paired Student *t* test (2-tailed) with an α of .05. For primary outcome 1, based on unpublished data ([name], personal communication, March 2025) in studies of human participants (βOHB whole-body R_a_: 10.4, SD 3.16 µmol/kg LBM/min). A sample of 15 participants has 80% power to detect a difference of 2.5 µmol/kg LBM per minute (25%), assuming a 2-sided α of .05, an SD of 3.16, and a correlation of 0.50.

For primary outcome 2, based on a study of 13 healthy volunteers conducted at the NIH Clinical Center (ClinicalTrials.gov NCT02719899) in which isolated CD4^+^ T cells were investigated, the mean paired refed–fasting differences in IL-17 release were 187.1 (SD 398.79) pg/mL, respectively [21]. Using a 2-tailed paired *t* test with an alpha of .05 (n=15), we will have 80% power, assuming an SD of the difference of 400 pg/mL to detect a clinically important TRE-induced change from admission in IL-17 of 311 pg/mL. We will attempt to recruit and screen in person up to 150 women and enroll 30 women to complete the study, including 15 lean women and 15 women with obesity.

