#### Outcome Analysis

Data will be analyzed with a statistical software package (eg, Stata [version 18; StataCorp]), with descriptive statistics presented as means (95% CIs), medians (IQRs), or percentages. Due to the pilot nature of this study, no prespecified covariates are assigned. Normality of data will be checked using the Shapiro-Wilk test and visually inspected using histograms. If severe violations of data normality are observed, transformations such as logarithmic or square-root transformations will be applied. If such transformations fail to generate normal data, we will pursue statistical analyses using nonparametric tests, which are conservative but less powerful.

Analysis of glucose levels, glycemic responses, and metabolic rates will be compared using paired 2-tailed Student *t* tests for within-group comparisons or unpaired 2-tailed Student *t* tests for between-group comparisons (lean women versus women with obesity). Statistical significance will be tested at an α level of .05. Quality control procedures will be implemented beginning with the data entry system, and data quality control checks will be run on the database. Any missing data or anomalies will be communicated to the relevant departments for clarification or resolution.

Study procedures will be subject to audits and monitoring visits to ensure compliance with the protocol and applicable regulatory requirements, consistent with the quality assurance program plan. Audit or monitoring visit results will be reported to the principal investigator for further reporting, as appropriate. Study documents and pertinent hospital or clinical records will be reviewed to verify that the conduct of the study is consistent with the protocol plan.

Circumstances that may warrant study termination or suspension include, but are not limited to, the following:

Identification of unexpected, significant, or unacceptable risks to participantsDemonstration of efficacy that would warrant stoppingInsufficient compliance with protocol requirementsData that are insufficiently complete and evaluableDetermination that the primary end point has been metDetermination of futility

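### Primary outcome 2 spans four cytokine families but is sized on IL-17 alone, with no lead variable or rule for when it is met

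*Protocol article*

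**What the plan says.** Under Sample Size Justification, the article lists two primary outcomes. The first is the change in βOHB rate of appearance. The second is the change in CD4+ T cell "responsiveness (T helper type 1, T helper type 2, Th17, and Treg cytokines", a list of four families with no cytokine marked as leading. On the test it says: "These outcomes will be evaluated using a 2-sided paired Student *t* test (2-tailed) with an α of .05".

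The power statement for the second outcome then narrows to one cytokine. It takes IL-17 release from an earlier study of 13 healthy volunteers, "assuming an SD of the difference of 400 pg/mL", and claims 80% power with n=15 "to detect a clinically important TRE-induced change from admission in IL-17 of 311 pg/mL". No SD or target change is given for any Th1, Th2 or Treg cytokine.

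Elsewhere the article does not narrow the definition. Primary Aim 2 (Study Aims) refers only to CD4+ T cell responses. Th17 is singled out in Secondary Aim 2, but for the comparison of lean women with women with obesity. Outcome Analysis repeats the .05 level, directly after describing glucose and metabolic-rate comparisons. It also lists the primary end point having been met among possible grounds for terminating or suspending the study.

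**The concern.** A paired t test handles one variable at a time. With four families and no composite, the natural reading is at least four tests that all carry primary status. The sample size belongs to only one of them.

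Two things follow. First, a reader of the final report cannot tell from this article which immune result was the primary one, so a chance change in one family could be presented under the primary heading. Second, the 80% power would be attached to an outcome of which it describes only one part. The reference to the primary end point being met sharpens the problem, because the article gives no way to decide when that is so for the immune outcome.

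**Working it through.** **Inputs** (Sample Size Justification): two-sided α = .05, n = 15, SD of the paired difference 400 pg/mL, change 311 pg/mL, four cytokine families. Correlations between cytokines are not given, so .3, .5 and .8 are assumed as a range.

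**1. The plan's own figure.** Paired t test, df = n − 1 = 14, noncentrality = (change / SD) × √n = (311 / 400) × √15 = 0.7775 × 3.873 = 3.01. Exact noncentral-t power is 79.9%, and the change detectable with 80% power is 311.2 pg/mL. The stated 80% and 311 pg/mL are correct for IL-17 as a single test at .05.

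**2. Four tests at .05, no true effect, independent.** 1 − 0.95⁴ = 1 − 0.8145 = 0.185, or 18.5%.

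**3. The same four tests, correlated.** Simulation of four equally correlated paired differences, n = 15, 100,000 replicates per setting:

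| Assumed correlation | Chance of at least one p<.05 |
|---|---|
| 0 | 18.8% (formula: 18.5%) |
| .3 | 17.3% |
| .5 | 15.9% |
| .8 | 11.7% |

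Even at .8 the figure is more than twice the nominal 5%. More than one cytokine per family, or separate tests in lean women and women with obesity, would raise it.

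**4. What each repair does to IL-17** (n = 15, SD 400, same power formula):

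| Rule | α for IL-17 | Power for 311 pg/mL | Detectable change at 80% power |
|---|---|---|---|
| IL-17 as sole immune primary | .05 | 79.9% | 311 pg/mL |
| Holm across βOHB R_a and IL-17, worst case | .05/2 = .025 | 69.0% | 351 pg/mL |
| Four families kept, Bonferroni | .05/4 = .0125 | 57.1% | 389 pg/mL |

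Only the first row keeps the power that the article states.

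**The case against.** The strongest reply has three parts.

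- **The article already points to IL-17.** The power statement is introduced as belonging to primary outcome 2 and calls the IL-17 change clinically important. The laboratory work under Immuno-Metabolomic Profiling and Study Design also centres on Th17. This is fair, and it is why the repair is only a clarification. But nothing in the article makes IL-17 the sole or lead primary variable, and the outcome definition says otherwise.
- **Multiplicity rules belong in the full protocol or analysis plan, which are not shown.** This stands for the adjustment method, and its absence here is not held against the article. The definition of the primary outcome, however, is stated here, and it does not match the calculation that follows it.
- **This is a pilot.** The calculations are described as feasibility estimates, and the findings as hypothesis generating (Strengths and Limitations). Strict family-wise control is therefore partly a matter of preference. Yet the article still labels outcomes primary, tests them at .05 and claims 80% power.

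A reader might also infer stronger points that the article does not support:

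- **That the immune primary succeeds if any one cytokine is significant.** No such rule is stated. The article gives no rule at all.
- **That the error rate is 22.6% or 40%.** These are 1 − 0.95⁵ and 1 − 0.95¹⁰. The first adds βOHB R_a, which is a separate aim. The second also assumes that every test is repeated in both strata. Both assume full independence.
- **That low power for the other cytokines causes false positives.** It does not. Any inflation comes from several unadjusted tests sharing primary status.

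**Conclusion.** The point holds as a mismatch between a stated primary outcome and its own sizing. Primary outcome 2 covers four cytokine families, the 80% power applies to IL-17 alone, and no lead variable or decision rule is named.

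The size is a chance of about 12% to 18.5% of at least one false positive, against 5%. This assumes one test per family in one sample of 15, no true effect, and correlations between 0 and .8. That each family is tested separately at .05 is the natural reading of the text, not its literal wording.

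Given the pilot framing, this is a cheap improvement and not a flaw that undermines the study.

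**What to change.** Before analysis starts, define primary outcome 2 as the change from day 1 to day 4 in IL-17 release from CD4+ T cells, with one two-sided paired t test at .05. Move the Th1, Th2 and Treg cytokines to secondary or exploratory outcomes and report them with confidence intervals.

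Add a sentence saying that βOHB R_a and IL-17 answer separate questions, each tested at .05. Holm across the two is optional. On the article's n=15 basis, its worst case raises the detectable IL-17 change from 311 to about 351 pg/mL and lowers power for 311 pg/mL to about 69%.

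The main change costs wording only and leaves the sample size and stated power untouched. The downside is that three families lose primary status. There is still time: the Results section says data analysis begins after all participants are recruited, and 20 of the planned 30 had been recruited by February 2026.
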